### Study procedures

#### Timeline

The Nurturing Moms study will assess the effectiveness of NurtureVR, a digital solution for maternal mental health, across four phases. In phase I, participants will be recruited from health clinics, community-based organizations, and online platforms. Interested individuals will receive a screening form link via REDCap to determine eligibility based on inclusion and exclusion criteria (described below). Eligible participants will be contacted by a study team member to review and electronically sign an informed consent form before completing a 10–20-minute baseline questionnaire on the same platform.

In Phase II, VR headsets will be shipped to participants one week after the baseline questionnaire is completed. Participants will use the NurtureVR for five weeks and will be asked to rate their level of stress, anxiety, mood, and pain level after each VR session using well-validated scales. In Phase III, participants will repeat the surveys three months after completion of the digital intervention. Additionally, two focus group sessions will be held with five participants each, focusing on Black and Latina expectant and postpartum women’s views on resilience, their NurtureVR experiences, perceptions, and recommendations for using VR for stress management. Each focus group will be conducted online to ensure accessibility, with one session scheduled before and one after the participants’ completion of the NurtureVR program. Discussions will follow a semi-structured format, encouraging open dialogue around key themes such as resilience and VR experience. For data analysis, we will employ thematic analysis, using NVivo software to organize and code responses. This approach allows for consistent identification of recurring themes, patterns, and variations in participants’ feedback, facilitating a thorough understanding of their experiences and recommendations. Coding will be iterative and conducted by multiple researchers to enhance reliability and capture diverse perspectives.

The final phase, which is optional, invites participants to repeat the surveys one year after completing NurtureVR. This comprehensive approach aims to provide a thorough evaluation of NurtureVR’s impact on maternal mental health in the short and longer term (See **Figure 1**).

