#### Statistical analysis plan

For the primary objective, General Linear Model procedures will be used to examine effects of Virtual Reality (VR) on stress over time among pregnant and postpartum moms. For the secondary objective, the User Experience Questionnaire and the Virtual Reality Neuroscience Questionnaire will be used to determine feasibility, usability, and acceptability of NurtureVR as an intervention. Measures of central tendency, and frequency distributions will be used for categorical data.

The main dependent measures will be continuous factors: maternal and pregnancy mental health and sleep scores (see **Table 1** for measures). Regression analysis will be used to explore whether sociodemographic factors (e.g., age, income, education), pregnancy factors (maternal experience scale) and postpartum factors (maternal experience scale and childbirth experience questionnaire) are associated with adverse mental and sleep health outcomes. In the statistical analysis, missing data will be handled using multiple imputation techniques to minimize bias and maintain the integrity of the analysis. Outliers will be identified through visual inspections of data distributions and statistical tests, and decisions about their inclusion will be based on their potential impact on the results and the underlying reasons for their occurrence. We will use sensitivity analyses to assess the robustness of findings. Adjustments for multiple comparisons will be made using the Bonferroni correction or false discovery rate (FDR) control to reduce the risk of Type I errors due to the number of outcomes being measured. Covariates such as age, parity (number of previous births), socioeconomic status, and baseline mental health status will be included in regression models to adjust for potential confounding factors and to provide a clearer understanding of the relationships between the intervention and outcomes. Only factors that show significant correlations in preliminary analysis will be entered in the final model. These data are significant as they will be used to generate effect size estimates (and sample sizes) for planned large-scale studies and to build preliminary exploratory models ascertaining factors that predict mental and sleep health outcomes among Black and Latina pregnant and postpartum women.

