### Data collection

#### Baseline and follow-up

After being screened and providing consent for the study, participants will receive an email with a link to complete the baseline survey online via REDCap. This survey includes questionnaires and well-validated scales that collect data on demographics, health history, stress levels, experiences of discrimination, sleep quality, emotional support, and overall pregnancy experience (see **Table 2**). Study team members may help the participant complete the baseline survey over the phone, on Zoom, or in person if necessary.

**Table 2 T2:** Study measures.

Variable*	Baseline	3 months	1 year
Tracking Form and Demographic Questionnaire	x		
Pregnancy Health History or Prenatal Screening Questionnaire (28)	x		
Perceived Stress Scale (29)	x	x	x
Everyday Discrimination Scale (Short Form) (30, 31)	x		
PROMIS^®^ Item Bank v1.0–Sleep Disturbance–Short Form 4a (32)	x	x	x
PROMIS^®^ Item Bank v2.0–Emotional Support–Short Form 4a (33)	x	x	x
Maternal Self-Efficacy Questionnaire (34)	x	x	x
Pregnancy Experience Scale (PES) (35)	x		
Childbirth Experience Questionnaire (CEQ) (36)	x		
Edinburgh Postnatal Depression Scale (EPDS) (37)	x		
User Experience Questionnaire (38)	x		
Virtual Reality Neuroscience Questionnaire (VRNQ) (39)	x		

*Some of these questionnaires have questions about the father. As the father is not relevant and is not a secondary participant in this study, these questions referring to the father have been removed.

Participants will be invited to complete the same survey three months following the completion of the intervention and will be monitored for 1 year. There will also be an optional 1-year follow-up (See **Figure 3**).

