### Study instruments

Tracking Form and Demographic Questionnaire: This form consists of two questionnaires to collect demographic information including age, race, and sex. The forms also capture socio-economic information such as employment, education, income, zip code, and other geographical data.Pregnancy Health History or Prenatal Screening Questionnaire: This 3-page questionnaire developed by the American Medical Association can provide useful material to researchers and physicians who want to gather information either prior to pregnancy or during a pregnancy. This form can help determine the risk of a baby having chromosomal conditions or neural tube defects based on the parents’ family history. The form captures past medical history of the father and mother, mother’s history of pregnancies, and exposures during pregnancy (28).Perceived Stress Scale: The perceived stress scale developed in 1983 is a 10-item questionnaire used to gauge stress levels in individuals aged 12 and older. It examines the degree to which situations are perceived as stressful in terms of how unpredictable, uncontrollable, and overloaded respondents find their lives. Score ranges from 0 to 40, with higher scores representing higher levels of stress. Average scores are calculated by adding up the scores and dividing by the number of items, providing a useful indicator for evaluating the overall level of agreement on the likert scale (where 0 = Never, 1 = Almost never, 2 = Sometimes, 3 = Fairly often, and 4 = Very Often) The perceived stress scale has been shown to have a coefficient alpha reliability of.84,.84, and.86 in three studied samples with a test-retest correlation of.85 (29).Everyday Discrimination Scale (Short Form): The everyday discrimination is a five-item instrument measuring experiences of daily discrimination followed by a question about what the person believes was the reason for that daily discrimination. Responses are coded on a 6-point Likert scale ranging from ‘never ‘= 1 to ‘almost everyday’ = 6. Responses are summed across items to produce a score ranging from 10 to 60 (40). The everyday discrimination scale, developed by David Williams in 1997, has shown high levels of internal consistency, convergent validity and divergent validity among African American men and women, and has been widely used in studies of discrimination and health (30, 31).PROMIS^®^ Item Bank v1.0–Sleep Disturbance–Short Form 4a: The PROMIS Sleep Disturbance and Sleep-Related Impairment item banks were developed using a rigorous and systematic methodology, including literature reviews, qualitative item review, focus groups, cognitive interviewing, and psychometric testing. The short form was developed from the full 27-item bank and has been shown to have convergent validity, construct validity, and reliability similar to the full bank. The short form is an 8-item form measuring the quality of sleep and sleep disturbance over the past 7 days. Four items use an intensity scale (not at all, a little bit, somewhat, quite a bit, very much), three items use a frequency scale (never, rarely, sometimes, often, always), and one item (S109) assessing overall sleep quality uses a scale of very poor, poor, fair, good, very good (32).PROMIS^®^ Item Bank v2.0–Emotional Support–Short Form 4a: The PROMIS Emotional Support Short Form was developed by domain experts from the full bank to capture the range of traits and allow researchers to study secondary outcomes without full additional measures. It consists of 4 statements assessing perceived feelings of being cared for and valued as a person. Responses are coded on a 5-point Likert scale ranging from 1 = never to 5 = always. The convergent validity has been supported by strong correlations between the PROMIS Emotional Support short form and measures of similar constructs. Discriminant validity has also been confirmed by negligible correlations between the emotional support measure and measures of dissimilar constructs (33).Maternal Self-Efficacy Questionnaire: The Maternal Self-Efficacy Questionnaire consists of 10 statements assessing mothers’ confidence in their ability to perform parenting-specific tasks such as understanding the baby’s needs and feelings, talking, reading to and playing with the baby, and taking the baby for regular clinic/doctor check-ups. Responses are coded on a 4-point Likert scale (1 = much worse, 2 = somewhat worse, 3 = as good, 4 = better than others). The questionnaire has been found reliable, face and content validity have been shown to be adequate as well as internal consistency and test–retest reliability for the assessment of maternal self-efficacy (34).Pregnancy Experience Scale (PES): The pregnancy experience scale consists of 10 statements measuring how much different aspects of pregnancy have made the mother feel either uplifted and happy or upset and negative. Each response is rated from 0 = not at all to 3 = a great deal. Internal reliability, test-retest reliability, and convergent validity were comparable to the original 41-item PES developed in 2004 (35).Childbirth Experience Questionnaire (CEQ): The childbirth experience questionnaire consists of 22 statements assessing four domains of the childbirth experience; Own capacity, Professional support, Participation, and Perceived safety. It evaluates women’s experience of labor and childbirth, including their perceptions and feelings. For 19 of the items the response format is a 4-point Likert Scale whereas the last three items use a visual analogue scale (VAS). The scoring range is 1 to 4 where higher ratings reflect more positive experiences. The CEQ has demonstrated internal consistency, discriminant validity, equal item-hypothesized scale correlation, and item equal variance (36).Edinburgh Postnatal Depression Scale (EPDS): The Edinburgh Postnatal Depression Scale developed in 1987 remains a prominent tool for measuring postpartum depression. It consists of 10 statements which identify signs and symptoms of depression in the postnatal period. Responses are scored 0, 1, 2, or 3 according to increased severity of the symptom. Items marked with an asterisk (*) are reverse scored (i.e., 3, 2, 1, and 0). The total score is determined by adding together the scores for each of the 10 items. The EPDS demonstrates acceptable sensitivity, specificity and positive predictive value. It has been used in many studies, and has been introduced as a valuable and powerful postnatal depression screening tool in different cultures (37).User Experience Questionnaire: The User Experience Questionnaire consists of 26-items measuring whether people find the using the NurtureVR product to be an overall positive or negative experience. A seven stage scale is used between two opposing descriptors of the user experience. Mothers rate more closely to the descriptor they identify with (38).Virtual Reality Neuroscience Questionnaire (VRNQ): The Virtual Reality Neuroscience Questionnaire consists of 20-item questionnaire measuring the quality of user experience, game mechanics, and in-game assistance, as well as the intensity of the VR induced symptoms and effects. Responses are coded on a 7-point Likert scale, ranging from 1 = extremely low to 7 = extremely high. The higher scores indicate a more positive outcome (39).

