#### Weekly mood state surveys

Once participants have completed baseline surveys, they will have a maternal health and wellness digital intervention (*NurtureVR* headsets) shipped to their homes. The VR box will include a QR code directly linked to mood state surveys via Google Forms. These surveys consist of four rating scales (see below) that subjectively measure participants’ anxiety, mood, pain, and stress levels before and after usage of the VR (see **Figure 4**). Participants will be asked to scan this QR code after each VR session to complete the surveys. They are encouraged to utilize the headsets as often as they wish, but at least once a week.

Anxiety Rating Scale: The anxiety rating scale is a 10-point pictorial Likert scale to measure mother’s feelings of anxiety ranging from 0 = Balanced Mood to 10 = Out-of-control behavior, self-harm (41). Each number corresponds to a face representing the visual level of anxiety. In adults, test-retest reliability of this scale has been used to measure consistency and stability. Analysis using a paired t-test found a significant difference (t(59) = -18.72, *p* <.001) between mean ratings of current and worse pain in the anticipated direction, suggesting that this measure reflects participants’ varying levels of pain (29).Mood Assessment Scale: The mood assessment scale is a 5-item pictorial scale to measure a mother’s overall mood. Each face corresponds to a mood ranging from very sad to very happy. The pictorial mood assessment scale has been shown to have internal consistency and convergent validity in assessing negative affect (42).Pain Scale: The pain scale is a 10-point pictorial Likert scale measuring experience of pain from 0 = no pain to 10 = worst pain. Accompanied by a Visual Pain Analog Scale with 6 pictures of faces corresponding to visual experiences of pain at 0, 2, 4, 6, 8, and 10 of the numerical pain scale. Reliability of the visual pain scale for acute pain measurement as assessed by intraclass correlation coefficients has been shown to be high and sufficiently reliable to assess for acute pain (43).Stress Scale: The stress scale is a 5-item pictorial Likert scale of faces to measure mother’s stress. Each face corresponds to the level of stress ranging from 0 = no distress to 5 = very severe. The stress scale has been shown to have convergent validity in assessing stress and negative affect (42).

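### Table 2 schedules the two user-experience questionnaires at baseline only, before any study headset is shipped, so as printed no score can reflect the 5-week programme

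*Protocol article*

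**What the plan says.** **Role in the analysis.** The Statistical analysis plan section says that "the User Experience Questionnaire and the Virtual Reality Neuroscience Questionnaire will be used to determine feasibility, usability, and acceptability of NurtureVR as an intervention". It names no other measure for those three outcomes.

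**Schedule.** Table 2 (Baseline and follow-up) has columns for baseline, 3 months and 1 year. The rows "User Experience Questionnaire (38" and "Virtual Reality Neuroscience Questionnaire (VRNQ) (39" are marked at baseline only. By contrast, "Perceived Stress Scale (29" is marked in all three columns.

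**Order of events.** In the Timeline section, "VR headsets will be shipped to participants one week after the baseline questionnaire is completed". The section on weekly mood surveys gives the same order: "Once participants have completed baseline surveys, they will have a maternal health and wellness digital intervention" sent to their homes.

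**Content of the forms.** Study instruments describes the UEQ as "measuring whether people find the using the NurtureVR product to be an overall positive or negative experience". The VRNQ covers user experience, game mechanics and in-game assistance, "as well as the intensity of the VR induced symptoms and effects".

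**Text pointing the other way.** Directly under Table 2, the article invites women to take the baseline survey again three months after the intervention ends. The Timeline says the surveys are repeated in Phase III.

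**The concern.** Both instruments ask about an experience that, on the printed schedule, has not yet happened. A woman who has not received the headset cannot rate the product, its in-game help, or symptoms that it caused.

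The Discussion calls feasibility and acceptability the primary aim and uses them to justify the sample size. It also says that user feedback will shape larger studies. If the forms are collected as tabulated, the standardised part of that evidence is lost. Analysis could not recover it: multiple imputation, which the article plans for missing data, needs some observed post-use values, and there would be none.

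**Working it through.** The plan gives no figure on this point. Its sample-size calculation concerns a one-sample t-test and has no bearing here. The check compares the schedule with the sequence of events.

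1. **Is the single mark a broken table?** Table 2 has 12 rows. Four are marked at all three times: the Perceived Stress Scale, the two PROMIS forms and the Maternal Self-Efficacy Questionnaire. The other 12 − 4 = 8 are marked at baseline only, including the UEQ and VRNQ. The table does separate repeated from baseline-only measures, so the mark reads as baseline.

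2. **Does baseline precede use?** Yes. Two sections agree that the headset goes out after the baseline survey, and one puts the gap at a week. The only earlier contact with the program is the demonstration offered at recruitment tables (Recruitment plan). It is optional, reaches only some women, and is not the 5-week home programme.

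3. **How many post-use administrations does Table 2 schedule?**
   - UEQ: 0 of 2 follow-up columns.
   - VRNQ: 0 of 2 follow-up columns.
   - Post-use scores expected from 50 women: 50 × 0 = 0 for each instrument.

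4. **Does the narrative supply one?** Taken literally, a repeat of the whole survey at three months would include both forms. But it would also repeat all 8 rows that Table 2 leaves unrepeated, among them the demographic form. The article's own description of the survey content in that section does not mention user experience. Table and narrative therefore disagree, and nothing in the article settles which governs. Even on the literal reading, the baseline administration stays in place, and the only usable one comes three months after use ended.

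5. **What else bears on the same aim?**

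| Source | Section | What it gives | What it does not give |
|---|---|---|---|
| Focus groups | Timeline | Views on NurtureVR; two sessions of five women, one of them after completion | Standardised scores |
| Administrative Control Panel | VR modules | Module start times, time stamps, completion status | Usability or symptom ratings |
| Session ratings | Weekly mood state surveys | Anxiety, mood, pain and stress | VR-induced symptoms |
| Adverse-event reporting | Data and safety monitoring plan | Reported events | A VRNQ symptom score |

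None of these is assigned to feasibility, usability or acceptability in the analysis section, and none replaces the two questionnaires. They do mean that the aim is not left without information.

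**The case against.** The strongest reply is that the article also says the survey is repeated at three months. Taken at its word, that gives the UEQ and VRNQ after use, so the table would simply be careless. This stands in part: it shows that the intent is unclear, and a reader who infers that the plan deliberately measures user experience only before use goes further than the text allows. It does not remove the problem, because the printed schedule says otherwise and the pre-use administration remains under either reading.

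A second reply is that the feasibility aim does not depend on these two forms alone. That is right. A reader might infer that the aim would yield no valid data, or that side effects of VR would go unseen. The documents do not support this: the post-programme focus group and the usage logs bear on feasibility and engagement, and adverse events are to be assessed and reported. What is lost is the UEQ and VRNQ scores.

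A third reply concerns the standing of the aim. The Introduction and Study design overview put stress and mental health symptoms first, and the analysis section places the two questionnaires under the secondary objective. Only the Discussion calls feasibility and acceptability primary. The scheduling error matters under either label, but its weight should not rest on the Discussion's wording alone.

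**Conclusion.** The point holds in this form: Table 2 places two post-use instruments at baseline only, and the surrounding text contradicts the table without resolving it. If Table 2 is followed, no UEQ or VRNQ score from any of the 50 planned women would describe the 5-week programme, and the analysis section's stated route to feasibility, usability and acceptability would have nothing usable to work on. Partial evidence on feasibility, engagement and tolerability would still come from the other sources.

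This assumes that Table 2 is the operative schedule and that a recruitment demonstration does not count as use of the programme. If the narrative governs instead, scores would exist at three months, and the remaining defects would be a meaningless baseline administration and a long recall interval.

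**What to change.** - In Table 2, remove the baseline mark for both the UEQ and the VRNQ and mark them at a time after use. The preferred point is an online form at the end of the 5-week programme, sent also to women who stop early, since they may have most to say about usability and symptoms. At minimum, use the existing 3-month survey.
- Name that time point in the Statistical analysis plan section.
- Reword the text under Table 2 and in the Timeline so that it lists the instruments actually repeated, in line with the table.

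**Cost.** The table and text edits are small, and each form is still given once. Table 2 has no end-of-programme column, so the preferred option adds one column and one online contact per woman. The 3-month option adds no contact, but it relies on recall three months after use.
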